#### Interim analyses

The interim test statistics will be conducted for the primary outcome. Two formal interim analyses are planned when 33% and 67% of the sample size are reached. The trial may be stopped for safety (*p* < 0.01) or effectiveness (*p* < 0.001) both evaluating the primary outcome (28-day mortality) but there will be no plans to terminate the trial for futility. We will account for alpha spending by the O’Brien-Fleming method and the final *p*-value will be considered at 0.048 [20].

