### Study population

All adult (adult ICU cut-off age) patients admitted to the ICU with suspected or confirmed COVID-19 by reverse transcription-polymerase chain reaction (RT-PCR) will be screened for eligibility. Inclusion criteria include acute hypoxemic respiratory failure (PaO_2_:FiO_2_ ratio < 200 despite supplemental oxygen with a partial/non-rebreathing mask at a flow rate of 10 L/min or above) with intact airway protective gag reflex and ability to follow instructions. Exclusion criteria include imminent intubation and the requirement for more than one vasopressor. A full list of inclusion and exclusion criteria is described in the published protocol [11]. Enrolled patients will be randomized using a concealed online system to helmet NIV with usual care or usual care alone at a 1:1 ratio. Usual care may include mask NIV, HFNO, or standard oxygen therapy. Randomization will be stratified by site. Helmet NIV will be delivered in pressure support mode, with initial settings of pressure support of 8–10 cm H_2_O, PEEP of 10 cm H_2_O with FiO_2_ of 100%, targeting flow rate of ≥ 50 L/min with an inspiratory rise time of 50 ms, and end flow/cycling off of 50% of maximal inspiratory flow. The settings can be adjusted according to the study protocol. The management of respiratory support in the usual care group including mask NIV is at the discretion of the treating team.

A flow diagram will be constructed according to the CONSORT guidelines (Fig. 1). We will report the number of patients who were screened, met inclusion or exclusion criteria, and were eligible but not enrolled with reasons for non-enrollment. We will report the number of patients who were randomized to each group, received the allocated intervention, withdrawn/lost-to-follow-up with reasons, and included in the final analysis.

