#### Primary outcome

The primary outcome is all-cause 28-day mortality. The primary outcome tests the primary hypothesis that helmet NIV reduces 28-day mortality (Supplement Table S3).

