### Statistical analysis

Details of sample size calculation have already been published in the study protocol [11]. The sample size of 320 provides a power of 80% to detect a 15% absolute risk reduction in 28-day mortality from 40 to 25%. Categorical variables will be reported as numbers and frequencies and will be compared between the study groups using the chi-square test or Fisher’s exact test. Continuous variables will be reported as means and standard deviations or medians and the first and third quartiles (Q1–Q3) and will be compared between the study groups using the Student’s *t*-test or the Wilcoxon–Mann–Whitney test, as judged appropriate by normality testing using Shapiro–Wilk test. For serial measurements (such as SaO_2_:FiO2 ratio, fluid balance, and serial SOFA), we will test the change over time and the difference between the two study groups over time using generalized linear mixed effect models by considering the link function of logit to incorporate the binary nature of the response variable and link function of log for score outcomes, with no imputation for missing values. To adjust for multiple testing for secondary outcomes and subgroup analyses, we will use the false discovery rate (FDR) as described by Benjamini and Hochberg [15]. We will report associations as relative risk (RR) or hazard ratio (HR) with 95% confidence intervals (CI) or beta coefficient and 95% CI as appropriate. We will compare dyspnea scores and device discomfort scores using generalized linear mixed models, incorporating fixed effects of treatment, time, and the treatment by time interaction and random effects of patient and center. Tests will be two-sided and at the 5% significance level. All statistical analyses will be conducted using the SAS software version 9.4 (SAS Institute, Cary, NC, USA). The statistical analysis remains blinded to the research team until completion of primary outcome data on the study population and will be performed by the study biostatistician. A summary of the analysis plan is provided in Table 1.

**Table 1 Tab1:** Summary of the analysis plan

Variables	Intention-to-treat cohort	Per-protocol cohort
Baseline characteristics	No statistical comparisons	None
Intervention and co-interventions	Chi-square, Fisher’s exact test, Wilcoxon–Mann–Whitney test, *t*-test as applicable	None

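### The named O'Brien-Fleming method, the fixed interim thresholds and the final level of 0.048 do not belong to one design; any excess over 5% is small and arises only on some readings

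*SAP article*

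**What the plan says.** The SAP section on interim analyses sets the schedule: "Two formal interim analyses are planned when 33% and 67% of the sample size are reached". It gives the stopping thresholds without distinguishing the two looks: "The trial may be stopped for safety (*p* < 0.01) or effectiveness (*p* < 0.001) both evaluating the primary outcome". On futility it says that "there will be no plans to terminate the trial for futility". It closes with the method and the final level: "We will account for alpha spending by the O’Brien-Fleming method and the final *p*-value will be considered at 0.048".

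The general statistical analysis section says: "Tests will be two-sided and at the 5% significance level". The primary outcome section gives the direction of interest: "The primary outcome tests the primary hypothesis that helmet NIV reduces 28-day mortality". The article does not say whether a stop for safety counts as rejecting the null hypothesis. It also does not say specifically whether the interim p-values are two-sided.

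**The concern.** Method, number and timing of looks, and overall alpha are all printed, and together they determine the O'Brien-Fleming final level. The printed 0.048 is not that level. The interim thresholds raise a second problem. O'Brien-Fleming bounds are very strict early and relax later, whereas the SAP uses one pair of thresholds at both looks.

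This has two practical consequences. A monitoring committee cannot follow both the named method and the printed thresholds. At the second look, an effectiveness p-value of 0.005 crosses the O'Brien-Fleming bound but not 0.001. At the first look, 0.0007 crosses 0.001 but not the O'Brien-Fleming bound. At the end, the level that decides whether the mortality result is called significant cannot be derived from the stated design.

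**Working it through.** **Inputs.** Overall alpha 0.05 two-sided (statistical analysis section). Looks at information fractions t = 0.33, 0.67 and 1, interim thresholds 0.001 (benefit) and 0.01 (harm), final level 0.048, no futility stop (interim analyses section). 320 patients randomized 1:1, so 160 per arm, with mortality of 40% vs 25% (statistical analysis and study population sections). I take the fraction of patients as the information fraction and treat the test statistics as normal.

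**Method.** Under the null, the sequential statistics Z_i are jointly normal with correlation √(t_i/t_j) for t_i < t_j. Overall error = 1 − P(lower_i < Z_i < upper_i at every look), evaluated numerically.

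**Step 1: reproduce 0.048.** The classical O'Brien-Fleming bound at look i is c/√t_i, with c solved so that overall error is 0.05.

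- One look at 50%: c = 1.977, final p = 0.0480. This matches the printed figure.
- One look at 33% gives 0.0497; one look at 67% gives 0.0451.
- Lan-DeMets spending with one look at 50% gives 0.0490.

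**Step 2: the looks actually planned.** Lan-DeMets spending uses α(t) = 4[1 − Φ(z/√t)] with z the 0.9875 normal quantile. Cumulative alpha spent is 0.00019 at 33%, 0.01235 at 67% and 0.05 at the end.

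| Version | p at 33% | p at 67% | final p |
|---|---|---|---|
| Classical (c = 2.0045) | 0.0005 | 0.0143 | 0.0450 |
| Lan-DeMets | 0.0002 | 0.0123 | 0.0462 |
| SAP, benefit | 0.001 | 0.001 | 0.048 |
| SAP, harm | 0.01 | 0.01 | 0.048 |

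Neither version gives 0.048, and neither gives constant interim thresholds.

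**Step 3: overall error with a final level of 0.048.** Two-sided p-values correspond to |Z| of 3.291 (0.001), 2.576 (0.01) and 1.977 (0.048).

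| Reading of the interim rules | Overall two-sided error |
|---|---|
| Stated thresholds, safety stop counts as a rejection | 0.0243 (benefit) + 0.0283 (harm) = 0.0526 |
| 0.001 in both directions | 0.0485 |
| Lan-DeMets interim bounds | 0.0517 |
| Classical O'Brien-Fleming interim bounds | 0.0528 |

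If a safety stop does not count as a rejection, the harm side can reject only at the final test. It then adds at most 0.048/2 = 0.024, so the total is at most 0.0243 + 0.024 = 0.0483.

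**Step 4: final levels that fit.** With the stated thresholds and safety stops counted, a final level of 0.0453 gives exactly 5%. With 0.001 in both directions it could be 0.0495. A final level of 0.045 gives overall error of 0.0497 (stated thresholds, safety stop counted), 0.0500 (classical) and 0.0489 (Lan-DeMets).

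**Step 5: power.** For the final test alone, power = Φ[(d − z·se0)/se1], with d = 0.15, se0 = √(0.325 × 0.675 × 2/160) = 0.0524 and se1 = √[(0.40 × 0.60 + 0.25 × 0.75)/160] = 0.0517. This gives 82.0% at 0.05, 81.6% at 0.048 and 80.8% at 0.045.

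**Step 6: a result in the gap.** With 160 per arm, 47 vs 64 deaths gives a chi-square p of 0.0459. That is significant at 0.048 and at the Lan-DeMets 0.0462, but not at the classical 0.0450. The chance that the final p falls between 0.045 and 0.048 is about 0.09% at 40% vs 40% mortality and 0.6% at 40% vs 25%.

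**The case against.** A reader might infer that the trial fails to hold its 5% error rate. The document does not support that as a general statement. The primary hypothesis is one of benefit, and under the printed thresholds the false-benefit error is 0.0243. The figure of 0.0526 arises only if a stop for safety is counted as rejecting the null, which the SAP does not say; the whole excess then lies on the harm side. The figures of 0.0517 and 0.0528 require replacing the printed 0.001 and 0.01 with O'Brien-Fleming bounds. This objection stands and limits the point to an inconsistency with a conditional and small effect on error.

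A reader might also see a contradiction between the general 5% level and 0.048. That is mostly a general rule followed by a specific one: the specific final level governs the primary outcome, and a cross-reference is enough. A 95% confidence interval beside an adjusted threshold is common practice and no error.

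Finally, the reference to alpha spending suggests the Lan-DeMets version, under which the 47 vs 64 example stays significant, and results in the gap are rare. That reduces the practical effect. It does not rescue 0.048, which neither version gives for the planned looks.

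**Conclusion.** The inconsistency is established without qualification: the printed final level is the classical O'Brien-Fleming value for one look at 50%, not for two looks at 33% and 67%, and the constant thresholds are not O'Brien-Fleming bounds.

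The excess over 5% is about 0.2 to 0.3 percentage points, and only if safety stops count as rejections or true O'Brien-Fleming interim bounds are used with 0.048. These figures assume two-sided interim p-values, the natural reading of the general rule. If the interim p-values were one-sided, error would be 0.0585 with safety stops counted, and a final level of 0.045 would still leave 0.0558 (0.0231 benefit + 0.0327 harm). Sidedness should therefore be stated. The sample size is not in question. This should be fixed before unblinding, but it is not critical.

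**What to change.** Name one boundary family and set the final level to match it. Either option is sound:

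1. Use O'Brien-Fleming bounds at both looks, with a final two-sided level of 0.045 (classical) or 0.046 (Lan-DeMets), and replace the fixed thresholds accordingly.
2. Keep the fixed thresholds and drop the O'Brien-Fleming label. State that the interim p-values are two-sided and whether a safety stop counts as a rejection. If it does, set the final level at 0.045. If it does not, 0.048 is already conservative and can stay.

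If the authors want one value that holds 5% on all the two-sided readings above, 0.045 does so. In the general statistical analysis section, note that the primary outcome is the exception to the 5% level.

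The cost is SAP wording and, at 0.045, a fall in power from 81.6% to 80.8%, still above the stated 80%. The sample size does not change.

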## Discussion

Several studies have investigated helmet NIV as a treatment for acute hypoxic respiratory failure [4–8]. A systematic review of RCTs and observational studies found that helmet NIV was associated with lower hospital mortality (odds ratio, 0.43; 95% *CI*, 0.26–0.69), intubation rate (odds ratio, 0.32; 95% *CI*, 0.21–0.47), and complications (odds ratio, 0.6; 95% *CI*, 0.4–0.92) compared with controls [21]. A meta-analysis of four RCTs (377 patients) showed that helmet NIV significantly increased the PaO_2_:FiO_2_ (+ 73.4; 95% *CI*, 43.9–102.9) and decreased the arterial CO_2_ levels, intubation rate (RR, 0.21; 95% *CI*, 0.11–0.40), and in-hospital mortality rate (RR, 0.22; 95% *CI*, 0.09–0.50) compared to standard oxygen therapy [22]. A network meta-analysis of 25 studies that included 3804 patients with acute hypoxemic respiratory failure for reasons other than COVID-19 found significantly lower intubation risks with helmet NIV compared with standard oxygen therapy [9]. The advantages of helmet NIV over other oxygen support modalities are thought to be more prominent in patients with COVID-19. This led to the design and conduct of multiple RCTs [10, 23]. Recently, one trial (*n* = 110) showed no difference in the number of days free of respiratory support at 28 days (primary outcome) between helmet NIV and HFNO [10].

The trial is unblinded given the nature of the intervention. The use of an objective, all-cause mortality as the primary outcome mitigates concerns regarding outcome assessment. The lack of blinding for the long-term quality of life outcomes is a limitation.

As the efficacy of helmet NIV to improve outcomes in severe acute hypoxemic respiratory failure due to COVID-19 pneumonia has not been established, the aim of the Helmet-COVID trial is to compare the effectiveness of helmet NIV compared to usual care on 28-day mortality in patients with acute hypoxic respiratory failure from COVID-19. The results of the trial and the possibility of contributing to individual patient meta-analysis would likely help address this important question.

## Trial status

The first patient was enrolled on February 8, 2021, and enrollment is expected to be concluded in November 2021.

## Conclusion

The Helmet-COVID trial evaluates whether helmet NIV improves the outcomes of critically ill patients with acute hypoxemic respiratory failure due to COVID-19. It is expected to provide evidence that will inform practice regarding the use of helmet NIV for respiratory support in these patients and contribute to future clinical practice guidelines.

## Data Availability

The dataset will be available from the corresponding author upon reasonable request in accordance with the regulations of King Abdullah International Medical Research Center, Riyadh, Saudi Arabia.

## Abbreviations

CI: Confidence interval
HR: Hazard ratio
ICU: Intensive care unit
IQR: Interquartile range
LOS: Length of stay
RT-PCR: Reverse transcription–polymerase chain reaction
RCT: Randomized controlled trial
RR: Relative risk
RRR: Relative risk reduction
SAP: Statistical analysis plan
